### Overview of the SIFT and ELFIN Trials

Speed of increasing milk feeds trial and ELFIN trials are funded by the HTA and managed by the National Perinatal Epidemiology Unit Clinical Trials Unit, Oxford, UK.^3^ Both trials recruit very preterm infants (<32 weeks gestation) in the first few days after birth while receiving care on a neonatal unit. The trial interventions complete prior to hospital discharge, although follow-up for SIFT continues until 2 years corrected age. SIFT recruited 2,804 infants and is powered to detect a clinically important difference in disability-free survival at 2 years, as well as having adequate power to detect a difference in the rate of the key short-term outcomes NEC and LOS. Infants were enrolled when stable, tolerating some milk (but less than 30 ml/kg/day), and when the attending clinician was ready to start increasing the amount of milk feeds. Infants were randomized to increases in milk feeds of either 18 or 30 ml/kg/day. Infants from multiple pregnancies (twins, triplets, etc.) were corandomized to the same treatment arm. It was anticipated that the speed of milk feed increases would result in full feeds (defined as at least 145 ml/kg/day) being achieved about 4 days later in the slower arm. This affects the duration of central venous access and use of parenteral nutrition, although this was not mandated in the SIFT protocol and therefore is likely to affect two key risk factors for LOS. The speed of milk feed increases may also affect exposure to breast milk in the first few days of life, a further risk factor for both LOS and NEC. SIFT is a trial of comparative clinical effectiveness and recognizes the possibility that there might be competing outcomes, i.e., there may be opposing impacts on NEC and LOS between the two trial arms (15). Hence, the use of disability-free survival as an outcome that takes this possibility into account. In addition, if there are no differences in key clinical outcomes (including neurological development), then data collected for health economic analyses may determine which regime is adopted in clinical practice.

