### Existing Mechanistic Evaluative Research of Feeding Rates and Supplemental Lactoferrin

Recent Cochrane systematic reviews of trials of early enteral feeding strategies for preterm infants have explored the role of trophic feeds, timing of introduction, and rate of increase in feed volume (22, 23), but none of these studies incorporated detailed mechanistic evaluation of gut function or microbiota. This might be important because alterations of gut microbes appear to be one of the key mechanisms involved in NEC or LOS pathogenesis (12, 13, 24–28). However, whether abnormal gut microbial communities are causative, or whether they simply reflect other processes involved in disease initiation is uncertain, and so can only be adequately explored in prospective trials. In the absence of a consistent causative agent in NEC studies, recent data demonstrate a specific microbial signature of high diversity and dominance of bifidobacteria that may be protective (28).

Breast milk is a complex biological fluid and differs from artificial formula milk in many respects. Components that differ include protein quality (including human lactoferrin), peptides and free amino acids, lipids (including long-chain polyunsaturated fatty acids), carbohydrates including human milk oligosaccharides (HMOs), cells, cytokines, and growth factors (e.g., insulin-like growth factor 1, epidermal growth factor, insulin, etc.). HMOs cannot be digested by the host, but rather act as growth substrates for specific *Bifidobacterium* spp. (29, 30). In the context of the SIFT trial, delayed initiation or slower increases in milk feeds reduce exposure to breast milk, which may affect gut epithelial development, function, and the pattern of gut microbiota.

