#### Late-Onset Sepsis

Microbiological culture of potentially pathogenic bacteria (including coagulase-negative staphylococci species but excluding probable skin contaminants) or fungi from fluid sampled aseptically more than 72 h after birth from blood or CSF, or clinically suspected sepsis (meeting three objective clinical criteria) AND intention for treatment for 5 or more days with intravenous antibiotics. If the infant died, was discharged, or was transferred prior to the completion of 5 days of intravenous antibiotics, this condition would still be met if the intention was to treat for 5 or more days.

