Select samples taken before disease onset at around 7–10 days after commencing the trial IMP (lactoferrin or placebo) in up to 60 infants per trial group so as to compare and assess microbial community changes between trial groups. Because other risk factors are also associated with disease (e.g., gestation, postnatal age, etc.), we will use progressive model building that investigates microbial community dynamics in relation to these covariates.Use multivariate ordination and classification approaches to quantify trial intervention group differences in gut microbial communities. This will (i) quantify the variation in microbial community composition before disease onset and (ii) develop suitable covariates describing microbial community variation for inclusion in statistical analysis as risk factors for disease.Use unconstrained ordination to investigate trends in community composition and to identify those microbial taxa from the NGS data that contribute most to community variation. These axes may be used as covariates in the subsequent analysis.Use constrained ordination to investigate the impact of trial intervention group on community variation prior to disease onset.Use divisive classification approaches to identify classes of microbial community among the cases. This will create a suite of categorical descriptors of community composition. Higher level community descriptors (diversity, evenness, rate of change in ordination score) will be derived in case the overall structure of the community is an important driver.In the interim analyses, we will determine whether there is any effect on the total microbial community differences or on individual bacterial taxa using MANOVA and consider a difference in the microbial community of *p* < 0.05 to be proof an effect. If the *p* value is between 0.05 and 0.1, we will consider this to be strong evidence of a likely effect, where statistical significance might subsequently be achieved in an analysis with larger numbers and/or greater numbers of diseased or high risk cases and will complete the study as planned. Regression models and SEM will adjust for potential confounding variables such as age, sex, gestation, and feed and antibiotic exposures.

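### Feed and antibiotic exposure are listed as confounders with no exception for randomised arm contrasts; in SIFT, adjusting for feed exposure would adjust for the intervention's own pathway

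*Protocol article*

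**What the plan says.** The Plan for Interim Statistical Analyses sets out to compare microbial communities between randomised groups. It closes with: "Regression models and SEM will adjust for potential confounding variables such as age, sex, gestation, and feed and antibiotic exposures". No exception is made for models in which trial arm is the term of interest, and the exposures are not limited to those before randomisation.

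The section on anticipated results for the microbiome and metabolome has canonical ordination quantify the influence of diet, age and the interventions together, as covariates of one analysis.

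The article gives its own account of how feed rate could act. In the overview of the two trials: "The speed of milk feed increases may also affect exposure to breast milk in the first few days of life". In the review of earlier mechanistic work: "slower increases in milk feeds reduce exposure to breast milk, which may affect gut epithelial development, function, and the pattern of gut microbiota".

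The arm tests named in the interim plan are different methods from those in the adjustment sentence. One item reads "Use constrained ordination to investigate the impact of trial intervention group on community variation prior to disease onset". Of the decision test, the plan says "we will determine whether there is any effect on the total microbial community differences or on individual bacterial taxa using MANOVA". No covariate set is given for either.

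**The concern.** The first hypothesis under Aims and Objectives is that the trial interventions change the gut microbiota, and the Statistical Analysis section lists the impact of the interventions among its four targets. The quantity needed is the total effect of being randomised to an arm. Randomisation already protects that contrast from confounding.

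An exposure that arises after randomisation and responds to the arm is a mediator. Conditioning on it does two things:

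- It removes the part of the effect that travels through it.
- It can create an association between arm and any unmeasured cause shared by the exposure and the microbiota. Illness severity is the obvious one, since sicker infants may be fed more cautiously and receive more antibiotics.

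In SIFT, feed exposure is the randomised factor itself. An adjusted null result there could be misread as showing that feed rate does not affect the microbiota. The Summary justifies the study by the weakness of observational work and the ability of trials to show causation. This adjustment would give up that advantage.

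**Working it through.** The plan gives no figure on this point, so there is nothing to reproduce. The check sets out where each exposure stands relative to the arm, then gauges the size under stated assumptions.

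**1. Which exposure lies on which path, according to the article**

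- *Feed exposure, SIFT:* on the path. Arms differ by design (daily increases of 18 or 30 ml/kg), and the two passages on breast milk exposure supply the link to the microbiota.
- *Feed exposure, ELFIN:* no passage says that lactoferrin changes it.
- *Antibiotic exposure, either trial:* no passage says that an intervention changes it. It can only be inferred. ELFIN aims to cut late-onset sepsis from 18% to 13%, and the clinically suspected form of the sepsis definition requires "intention for treatment for 5 or more days with intravenous antibiotics". For SIFT, feed rate is said to bear on risk factors for sepsis.

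**2. How closely SIFT arm and feed volume move together**

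Inputs from the article: increases of 18 or 30 ml/kg/day, a starting volume below 30, full feeds at 145. Assumed: starting volume uniform on 0 to 30, volume capped at 145, and achieved rates varying log-normally with log-scale SD 0.1, 0.3 or 0.5. Cumulative volume was simulated to day 3, 5, 7 or 10. The variance inflation factor is 1/(1 − r²).

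| Log-scale SD of achieved rate | r (arm, cumulative feed) | Variance inflation |
|---|---|---|
| 0.1 | 0.77–0.85 | 2.5–3.7 |
| 0.3 | 0.58–0.62 | 1.5–1.6 |
| 0.5 | 0.42–0.44 | 1.2–1.3 |

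**3. What adjustment would do to a SIFT contrast**

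Assumed: total effect 0.5 SD; 50 infants per arm (the article expects about 100 SIFT infants and 25 to 50 per arm analysed); residual variance unchanged by adjustment; two-sided 5%; normal approximation.

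- Unadjusted: SE = √(2/50) = 0.20. Power = Φ(0.5/0.20 − 1.96) = Φ(0.54) = 0.71.
- Adjusted, r = 0.6: SE = 0.20/√(1 − 0.36) = 0.25. Effect = 0.5 × (1 − mediated share).
  - 10% mediated: Φ(0.45/0.25 − 1.96) = Φ(−0.16) = 0.44
  - 25% mediated: Φ(0.375/0.25 − 1.96) = Φ(−0.46) = 0.32
  - 50% mediated: Φ(0.25/0.25 − 1.96) = Φ(−0.96) = 0.17
- If all of the effect is mediated, the adjusted effect is 0.

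**4. Bias through a shared cause**

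All values assumed: arm shifts feed exposure M by 1; M shifts the microbial score by 0.5; an unmeasured factor with variance 1 affects both with coefficient 0.5; no direct arm effect. The total effect is 1 × 0.5 = +0.50. Adjusted for M, the arm coefficient is −(0.5 × 0.5)/Var(M within arm).

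- Var(M) = 1: −0.25
- Residual SD of M = 1, so Var(M) = 0.25 + 1 = 1.25: −0.20

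A change of sign is therefore possible. No figure in the article says how likely it is.

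**5. ELFIN, through antibiotics given for sepsis**

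Mean sepsis rate = (0.18 + 0.13)/2 = 0.155. Arm–sepsis correlation = 0.05/(2√(0.155 × 0.845)) = 0.069, so r² = 0.005. If such antibiotics shift the score by an assumed 0.5, 1.0 or 1.5 SD, the part adjusted away is 0.05 × that shift: 0.025, 0.05 or 0.075 SD. In samples taken before disease onset it should be smaller still.

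**The case against.** The strongest reply is that the adjustment sentence concerns another kind of model. It sits in an analysis of ELFIN infants only ("Select samples taken before disease onset at around 7–10 days after commencing the trial IMP (lactoferrin or placebo) in up to 60 infants per trial"), whereas the feed-pathway evidence is all about SIFT. The regression and SEM can be read as the disease-risk models described elsewhere in the article, where feed and antibiotics are proper confounders. The article also plans to use SEM to separate direct from indirect effects, which reports a mediated effect instead of deleting it. The list is introduced as examples, and exact covariate sets commonly go in the analysis plan.

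Much of this stands, and it rules out three stronger readings that a reader might infer.

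- *That the plan says both interventions change both exposures.* It says so only for feed exposure under SIFT.
- *That the interim continue-or-stop decision rests on adjusted models.* The decision test is MANOVA, with no stated adjustment. The plan does say "we will use progressive model building that investigates microbial community dynamics in relation to these covariates", but the examples it gives are gestation and postnatal age.
- *That the lactoferrin effect would be wholly adjusted away.* The only route that can be inferred, sepsis antibiotics, is weak.

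The reply does not dispose of the point. The sentence closes a plan for comparing randomised groups and covers regression as well as SEM. It calls these exposures confounders and exempts no arm contrast. The direct and indirect effects planned for SEM are those of risk factors on disease incidence, not of arm on microbiota. The canonical ordination puts diet beside the interventions in the main analysis, which is not confined to ELFIN. This is a stated choice, not a detail left open.

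**Conclusion.** The point holds in a limited form. The article prescribes adjustment for feed and antibiotic exposure without separating arm-effect models from disease-risk models. A team following the text could therefore obtain a SIFT arm estimate that is not the total effect its first hypothesis calls for.

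For SIFT the loss could be large or complete, because arm and cumulative feed volume plausibly correlate at 0.42 to 0.85. The power figures and the possible sign change illustrate the mechanism under assumed effect sizes, mediated shares and residual variances; they are not predictions. The SIFT part of the study is about 100 infants.

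For ELFIN the objection is one of principle, and the likely loss is small. The documents do not support a conclusion that the interim decision or the lactoferrin comparison is invalid.

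**What to change.** State the covariate set by type of model:

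- **Randomised arm contrasts** (regression, the total effect from SEM, constrained or canonical ordination; interim and final): adjust only for variables fixed before randomisation, such as gestation and sex, plus postnatal age at sampling. Do not enter feed, diet or antibiotic exposure.
- **Mediation analyses:** use feed and antibiotic exposure here, labelled as non-randomised comparisons that assume no unmeasured shared causes. Do not present a direct path as the arm effect.
- **Disease-versus-control models:** keep feed and antibiotic exposure as confounders, counted only up to the time of the sample.

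Add one sentence saying whether the interim MANOVA is adjusted and, if so, that the first rule applies. The cost is wording only: the variables are already named in the plan, and neither sampling nor sample size changes.

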## Summary

The MAGPIE study provides a unique opportunity to explore the interaction between nutritional and feeding interventions on gut microbiota in early life in preterm infants, and within the context of large randomized trials. Next-generation sequencing and metabolomic techniques produce large datasets that require complex modeling in order to present findings of clinical relevance. While these new “omic” techniques have provided unique insights into complex multifactorial diseases such as NEC, current studies are limited by their observational nature and are at significant risk from type I errors due to residual confounding and/or reverse causation. Prospective trials are needed to determine direct causation due to clinical interventions such as milk feed rate or enteral lactoferrin supplementation. Nesting mechanistic evaluation within these trials using non-invasive and safe sampling increases the value of large RCTs. This may produce important new data of diagnostic and therapeutic relevance or identify differences in responses between groups of infants (i.e., exploring in what setting interventions may be most or least efficacious), as well as potentially providing information about risk stratification for future studies. NEC and LOS remain extremely prevalent and serious diseases in preterm infants and both are associated with considerable mortality and morbidity, as well as generating significant health-care resource costs. Studies such as MAGPIE will improve our understanding of the basic biology of health and disease and the role of early life gut microbiota colonization in a high risk group of patients where mechanistic understanding is limited.

## Ethics Statement

This study received research ethics approval from East Midlands—Nottingham 2 Research Ethics Committee 16/EM/0042.
